## Abstract

As veganism becomes more popular, the number of vegan pregnant women and children is steadily increasing. During vegan pregnancy and early childhood, there is a high risk for nutrient deficiencies that may impair child development. External factors, such as healthcare advice, social networks, and social environments, that affect the diet of vegan pregnant women, parents, and their children, as well as their approach towards dietary supplementation, have not yet been investigated. Various sources of information, combined with a lack of expertise, sparse food and nutritional health literacy, and qualitatively heterogeneous information provision by medical experts, unsettle vegan pregnant women and parents and affect their dietary choices and potentially the health of their children. The VedieS study aims to investigate potential connections between external influences and associated impacts on a vegan diet and the intake of dietary supplements (DS) of pregnant women and children. Two surveys are being conducted within the study: one targeting 1000 vegan pregnant women and parents, and another targeting 60 experts in each of five healthcare groups: gynecologists, pediatricians, general practitioners, pharmacists, and dietitians. This study is the first to examine how socio-economic, social, and further informational factors influence dietary practices during vegan pregnancy and childhood. It highlights the need for reliable, expert-led guidance, as current information sources are often inconsistent and may put these vulnerable groups at risk.

## 1. Introduction

During intensive development phases, such as pregnancy and childhood, the probability of insufficient nutrient supply rises [1]. In the course of a vegan diet, the focus should be on an adequate supply of vitamin B12, zinc, iron, calcium, vitamin D, iodide, and omega-3 fatty acids [2,3,4,5]. Nutrient deficiency can be prevented by supplying these critical nutrients of a vegan diet adequately, with specific foods or with DS [6,7,8]. A vegan diet is defined as a dietary pattern that excludes all animal-derived products—including meat, fish, dairy, eggs, and honey—and is based on the consumption of plant-derived foods such as fruits, vegetables, grains, legumes, nuts, and seeds [9]. A purely plant-based diet can provide all necessary macro- and micronutrients during pregnancy and childhood, except for a possible lack of docosahexaenoic acid (DHA) and eicosapentaenoic acid (EPA), as well as vitamin B12 [10]. Newborns of vegan mothers are on average smaller (small for gestational age) and are often born with a lower birth weight than those born from omnivores [11,12], which could lead to further nutrient-deficiency-related development and health impairments. If mothers lack an adequate supply of nutrients in their diet, nutrient deficiencies can occur in infants despite breastfeeding [13,14,15,16,17,18,19]. Expert groups such as the Academy of Nutrition and Dietetics (AND), the German Nutrition Society (DGE), and the Austrian Nutrition Society (OEGE) partly disagree about the risks of a purely plant-based diet for pregnant women, infants and children [20]. The AND considers a well-planned vegan diet to be safe, even during vulnerable stages such as pregnancy and childhood [21]. Although the DGE neither clearly supports nor rejects a vegan diet during the mentioned life phases, it points out insufficient data and the need for comprehensive nutritional skills for safe implementation [22]. The OEGE does not recommend a vegan diet during pregnancy and childhood due to the risks of possible malnutrition and possible associated impairments [23]. All organizations share the common point of view that a vegan diet during life phases such as pregnancy, infancy and childhood should be preceded by comprehensive planning with special emphasis on critical nutrients of a vegan diet—especially vitamin B12 supplementation. In the past no distinct statements were made on the benefits or drawbacks for vegan pregnant women and their children in terms of nutrient supply, due to a lack of studies with a sufficiently large number of participants or inadequate significance [24,25,26]. The latest findings show that there are risks of malnutrition, which can be prevented by the use of DS and observing the health and developmental status of mother and child [27,28]. Although the selection of vegan foods is becoming more diverse, there is no data on whether this expansion of what is on offer results in a better nutrient supply for vegans—the current state of studies suggests dietary supplementation is necessary [29,30,31]. Pregnant women who consume an omnivorous diet usually take DS to support the healthy development of their unborn children [32]. Influential factors that affect the approach of vegan pregnant women and parents towards DS have not yet been scientifically determined. It has been shown that mothers of vegan-fed children have less nutritional knowledge than mothers whose children follow an ovo-lacto-vegetarian diet [33]. Parents frequently ask pediatricians how to provide the most balanced diet for their children [34,35]. For this reason, constructive communication between parents of vegan-fed children and their pediatricians and dieticians is important to make comprehensive information about a healthy, purely plant-based diet available [36,37]. Despite frequent uncertainty about the safety of DS due to varying production standards regarding different origins and manufacturers, the market for supplements and botanicals is expanding [31]. Compared to pharmaceuticals, DS are subject to food law and are, therefore, liable to less strict controls [38]. An official approval process, that is required for pharmaceuticals and takes many years, is not obligatory for DS. This can have an impact on the safety and harmlessness of their consumption. Preparations that consumers buy online are often of inferior quality. Ingredients are inadequately declared and can even be detrimental to the health of consumers because of different regulations in different parts of the world, which is why customers and patients should be comprehensively informed by medical experts [39]. Additionally, adulterations can cause harmful health impacts [40]. Non-prescription DS compared to prescription DS are often characterized by insufficient information on ingredients, dosage and intake [41]. This represents a major risk, especially for pregnant women and children [42]. The relationship between vegan parents and especially physicians can, therefore, influence the health and well-being of vegan-fed children. However, the majority of pediatricians is perceived skeptical or negative towards a vegan diet, which can affect vegan parents’ trust in their children’s physicians and limit or prevent communication [34,43]. Many parents do not inform pediatricians about their children’s vegan diet in order to avoid being exposed to criticism [34]. A skeptical attitude of physicians could result from legitimate, nutrition-related objections on the one hand and from a lack of knowledge about a vegan diet and DS on the other [44]. This can lead to health impairments for vegan pregnant women and children due to a lack of information supply and miscommunication. It is not yet clear whether other specialists and medical experts, in addition to pediatricians, have a negative attitude towards a vegan diet during pregnancy and childhood and, therefore, offer little or no advice on vegan diets and DS. If a negative attitude also exists among gynecologists, general practitioners, dieticians and pharmacists, this could have a negative health- and nutrition related effect on vegans due to a lack of information transfer. The level of information and the associated information provided by medical experts on a vegan diet and DS during pregnancy and childhood, therefore, has a significant impact on the adequate nutrient supply of vegans. The level of knowledge among medical experts regarding a vegan diet and DS has not yet been sufficiently examined. Competent advice on supplementation with DS is essential for a healthy development during pregnancy and childhood. If information is not provided by medical experts, vegans use other sources of information, particularly social media. It can be assumed that many vegans are insufficiently, incorrectly or not at all informed about DS and a well-balanced vegan diet due to the different quality of disposable information. Dubious sources of information and influential factors (e.g., social environment, internet and social media, magazines, advertisement) are likely to make parents feel insecure and can affect the health of their children. A lack of expertise on the part of vegan pregnant women and parents (on a vegan diet and DS) and insufficient support from medical experts (pediatricians, gynecologists, general practitioners, pharmacists, dieticians) entail possible health risks. The impact of medical expertise and other social, sociodemographic factors (e.g., age, social environment and background, internet and social media, advertising), on the diet of vegan pregnant women and children (up to the age of 5 years), as well as on supplementation with DS needs to be investigated. Whether and to what extent external factors influence a vegan pregnancy, infancy and childhood have not yet been comprehensively investigated. In addition, there is still no data on the opinion and level of knowledge of consulting medical experts and associated consequences regarding nutrition and the possibility of supplementing DS for vegans.

Previous studies that investigated vegan diets during pregnancy and early childhood focused either on medical risks or aspects such as parents’ knowledge about a vegan diet or DS intake. Kostecka et al. [33] found that parental food and nutritional health literacy plays a central role in ensuring safe vegetarian diet for children, especially regarding the correct use of DS. Palma et al. [5], Sebastiani et al. [7] and Papadopoulou et al. [45] show that a well-planned vegan diet can be suitable during pregnancy. However, careful medical monitoring of micronutrient intake is necessary, which highlights the importance of advice from medical experts. Nevertheless, these studies do not fully consider the social and behavioral factors that can influence parental decisions. The VedieS study addresses these gaps by investigating how external factors (e.g., criticism from medical experts, lack of advice, use of non-professional information sources) influence dietary behavior and DS use among pregnant vegans and parents of vegan children. A study by Bivi et al. [34] showed that many vegan parents reported that they do not feel sufficiently supported by their pediatricians. Instead, many relied on online platforms (e.g., social media) or advice from peer groups to decide whether to take or administer DS. The VedieS study aims to examine how factors such as trust in expert advice, perceived barriers regarding effectiveness of DS, and social expectations can influence vegans’ adherence to supplementation recommendations and maintenance of their diet during sensitive life stages such as pregnancy and childhood. Furthermore, little is known about medical experts’ perspective on this issue. A recent study from France [46] found that many pediatricians and dieticians feel unprepared to advise vegan families. Some even have negative attitudes toward a vegan diet. By including both vegan participants and medical experts in our survey, we want to examine whether such attitudes lead to less effective counseling, inconsistent advice, lower patient trust and consequently to possible health risks. Understanding these connections is important to improve communication and to provide reliable, competent support for vegan parents and pregnant women. Previous research has primarily focused on food and nutritional health literacy or the medical impact of a vegan diet. Our study is one of the first to examine how social environment, information sources, and trust in medical experts influence DS use and dietary behavior in vegan families during pregnancy and early childhood. The findings can help explain behavior patterns and support medical experts in their advisory role.

The VedieS study is based on several research hypotheses that examine how external factors influence the dietary behavior of vegans during pregnancy and early childhood. We hypothesize that pregnant vegans and parents of vegan-fed children often seek information and support from other vegans, peer groups, or social media but not from medical experts. This is especially important when medical advice is lacking or perceived negatively towards a vegan diet. We also hypothesize that critical or unclear advice from medical experts may lead to uncertainty, fear of nutritional deficiencies, or the use of unreliable information sources. In some cases, this could result in dietary changes or incorrect use (or even avoidance) of DS. Another hypothesis is that inadequate communication about the use of DS, particularly about the administration of DS to children (e.g., dosage, dosage form), may lead to inconsistent use or misunderstandings, thus increasing the risk of health risks. It is also assumed that many vegan parents have difficulties to clearly distinguish between DS, food, and medication—especially when they receive unclear advice from medical experts or insufficient advice. Finally, while many vegans consider their diet to be generally healthy, they also recognize the importance of DS during pregnancy and early childhood. However, the decision to take DS may be more influenced by social or emotional factors than by scientific reasons. These hypotheses form the basis of the study and shape the development of the survey, the research questions and the planned analysis.

### Theoretical Framework

The theoretical framework of the VedieS study is based on two models from health psychology: it combines the Health Belief Model (HBM) and the Theory of Planned Behavior (TPB), as shown in Figure 1. These models can help to explain how pregnant vegans and parents of vegan-fed children make decisions about their diet and DS use during pregnancy and early childhood and can help to understand how views and communication of medical experts can influence their decisions. The HBM focuses on individuals’ perceptions of health risks (e.g., nutrient deficiencies of vitamin B12 or calcium), as well as the perceived benefits and barriers related to DS intake. For instance, if vegans feel criticized or not adequately supported by medical experts, they may lose confidence in their advice and instead turn to less reliable sources, such as social media or peer groups (e.g., other vegans, friends). Studies have shown that the HBM can help to predict behavior related to diet and DS use, particularly among pregnant women [47,48]. The TPB describes the factors that shape people’s intentions to act. It considers their attitudes toward DS, the influence of others (e.g., family, friends, medical experts), and whether they feel capable of managing their diet and supplement use. This becomes especially relevant when vegans are seeking trustworthy dietary advice. TPB has been used in previous research to explain motivations for plant-based diets and supplement intake [47,49]. For these reasons, both models served as the basis for designing the VedieS study and developing the questionnaires. Items for both groups (vegans and medical experts) were grounded in the main principles of HBM and TPB, which include perceptions of risks and benefits, social influences (e.g., pressure, support), and confidence in managing DS-related decisions (e.g., dosage, administration). This approach is supported by recent studies [33,34,46], which highlight the importance of trust, attitudes, and access to comprehensive information among vegans and vegetarians. These findings provide further justification for using the HBM and TPB as the theoretical framework for the VedieS study.

## 2. Materials and Methods

### 2.1. Objective

The aim of the descriptive, cross-sectional VedieS study is to investigate, for the first time, the factors influencing vegan parents and pregnant women in adhering to a strictly plant-based diet and in their use of DS, as well as the potential implications for their health and the health of their children up to five years of age. External factors that lead to and influence the development of individual food and nutritional health literacy and the use of DS by vegans are the main research questions. Hence, this approach focuses on the relevant information sources for vegans as the main cause of their food and nutritional health literacy. Not only vegans themselves but also medical experts (pediatricians, gynecologists, general practitioners, pharmacists, dietitians) are being asked about their opinion, knowledge and advice on a vegan diet, to be able to draw conclusions about the quality of information they provide to vegan parents and pregnant women.

Influential factors, sources of information gathering, reasons to choose certain DS, difficulties in administering DS to vegan-fed children (up to the age of 5 years), as well as details about the compliance of DS intake of vegan pregnant women and parents, should be revealed. The results can serve as a starting point for comprehensive information provision for vegans and provide insight into their food and nutritional health literacy. The opinion of medical experts has a decisive influence on the health of vegans. For this reason, the content of their advice will also be assessed as the advisory role of the medical experts is essential to provide vegans with reliable information on a balanced vegan diet and use of DS.

Current medical advisory conditions and sources of information for vegans are being examined in detail. The obtained results can indicate the importance of comprehensive advice from medical experts and the prevention of health risks for pregnant vegans and parents of vegan-fed children. Therefore, the study aims to highlight that a balanced, purely plant-based diet for pregnant women and children depends mainly on advice from physicians, pharmacists and dieticians. A comprehensive specialist knowledge about a vegan diet and DS among medical experts is the basic prerequisite for competent information provision and as a result essential for a low-risk vegan pregnancy and childhood. The study results are intended to encourage medical experts to provide comprehensive advice to vegans to be able to support pregnant women and parents of vegan-fed children as best as possible during these vulnerable life stages. As the number of vegans is constantly increasing, expertise about a vegan diet and DS should be expanded among physicians, pharmacists and dieticians and made permanently available.

For this reason, the following objectives were defined:

#### 2.1.1. Primary Objectives

##### Determination of Main Influential Factors That Affect Vegans Regarding Their Diet During Pregnancy and When Feeding Their Children (Up to the Age of 5 Years)

Influence by medical experts or other influences (e.g., social environment, Internet and social media, magazines) concerning the decision for or against a vegan diet should be clarified. Depending on the source of information, the possible risks of a vegan diet during pregnancy, infancy and early childhood can be misjudged.

The identification of information sources for vegans on dietary supplements, as a reason for the approval or rejection of DS (during pregnancy, infancy and early childhood), embodies trustworthiness by ranking.

It should be determined which information on DS (during pregnancy, infancy and early childhood) is used and whether this information appears trustworthy or causes uncertainty. Information received affects selection, intake, or avoidance of certain DS. The health impact of selected sources of information on DS can be made visible. Medical expert advice and other opinion-forming aspects (e.g., social environment, Internet and social media, magazines) should be ranked according to their relevance. Main sources of information should be identified.

This can be an important approach for the improvement of information supply on DS in a vegan diet and for minimizing risks preventively. By recognizing sources of information classified as the most important for vegans, the main causes of frequent inadequacies in the provision of information could be identified and if necessary, positively changed.

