### 2.5. Questionnaires

Participants are forwarded the scientific survey via a link/URL. The questionnaires can be answered at any time and from any chosen location via LimeSurvey [50] (LimeSurvey Cloud Version 6.6.7) using a tablet, PC, laptop, or smartphone. The questionnaires used in this study are provided in the Supplementary Materials. The survey tools were developed specifically for this research question and are grounded in the ideas of the Health Belief Model (HBM) and the Theory of Planned Behavior (TPB). These theoretical models served as a basis to define research questions and hypotheses and to develop questionnaire items. Two online surveys were developed: one for vegan participants (pregnant women and parents of vegan-fed children) and one for medical experts (physicians, pharmacists, and dieticians). All participants in each target group received the same version of the respective questionnaire. Within the survey for vegan participants, there are 10 question categories and corresponding detailed questions on the following: health (A), definition and reasons for a vegan diet (B), definition and understanding of and about DS (C), benefits, risks and expectations of DS (D), personal selection criteria of DS (E), level of knowledge about DS (F), sources of information about a vegan diet and DS (G), influential factors regarding a vegan diet and DS (H), deficiency and dosage of DS (I), and administration and compliance with DS intake (J). The questionnaire categories for the medical experts are structured similarly, but with a focus on topics related to patient and client counseling, as well as the personal views of physicians, pharmacists, and dietitians regarding a vegan diet and the intake of DS during pregnancy and childhood. Both questionnaires contain Likert scales, multiple-choice and single-choice questions, ranking questions, and an open-ended item. While most of the used response formats are common in surveys, the actual items were newly developed for the VedieS study. Because the questionnaires were developed based on the theoretical framework and objectives of the study itself, no standardized or pre-validated instruments were used, so no external approval was required. No additional statistical validation methods (such as factor analysis) were planned, as the questionnaires were not designed as psychometric tests but as data collection instruments based on the study hypotheses. To ensure content validity, a pre-test was conducted. The questionnaire was reviewed by nutritional experts, and a pretest was conducted with individuals from the target groups (vegans *n* = [20.0], medical experts *n* = [10.0]). This pretest focused on comprehension, relevance, and completion time of the items. Due to the received feedback, minor modifications for improvement were made. On average, completing the questionnaire took approximately 25 min for vegan participants and 20 min for medical experts.

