## 3. Results/Outcome Measures

### 3.1. Primary Outcome Measures

Primary outcome measures include influential factors that affect how vegans approach their diet during pregnancy. Furthermore, details about decisions regarding the use of DS of vegan pregnant women and parents’ administration of DS to their children, which impacts their nutritional status and health, are essential outcomes.

Other primary outcome measures involve methods of information gathering related to a vegan diet and DS among vegans, as well as opinions and recommendations from medical experts on these topics and their advice to support or reject a vegan diet and DS. All findings will be based on the frequency and prevalence of collected responses.

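### A primary objective reads causes of inadequate information from the sources vegans rate as most important, but importance and trust ratings do not measure adequacy

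*Protocol article*

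**What the plan says.** The first primary objective in section 2.1.1 covers the sources that shape vegans' decisions on diet and dietary supplements (DS). Medical advice and other opinion-forming influences "should be ranked according to their relevance", and the objective also asks "whether this information appears trustworthy or causes uncertainty". It closes with an inference. The premise is "By recognizing sources of information classified as the most important for vegans"; the conclusion is that "the main causes of frequent inadequacies in the provision of information could be identified and if necessary, positively changed".

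Section 2.1 uses similar causal language: "this approach focuses on the relevant information sources for vegans as the main cause of their food and nutritional health literacy". Section 3.1 says of the primary outcomes: "All findings will be based on the frequency and prevalence of collected responses". Sections 2.1 and 2.2 describe the design as descriptive, explorative and cross-sectional.

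Other parts of the article bear on adequacy:
- Section 2.5 lists question blocks in the vegan survey that include "level of knowledge about DS (F), sources of information about a vegan diet and DS (G), influential factors regarding a vegan diet and DS (H"). Block I covers deficiency and dosage.
- Section 2.1.2 makes vegans' knowledge of DS, deficiency risk and dosage a secondary objective.
- Section 2.1 says medical experts are surveyed "to be able to draw conclusions about the quality of information they provide to vegan parents and pregnant women", and section 2.1.1 makes their opinions and knowledge a primary objective.
- Section 2.7 lists people with professional advice against people using informal sources as a possible comparison.

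**The concern.** The closing sentence moves from which sources matter most to respondents to which sources cause inadequate information. These are different quantities. A source can rank first because it is widely used and good, or because it is widely used and poor, and the ranking looks the same in both cases.

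The objective adds that the identified causes may be changed for the better. If the sentence guided the report, efforts to improve information could be directed at a source whose users are well informed, while a less popular but poorer source is passed over. The word cause raises a second problem. Even if adequacy were measured, a single cross-sectional survey could show only that users of a source know more or less. It could not separate the effect of the source from the kind of person who chooses it.

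**Working it through.** The plan gives no figure on this point, so there is none to reproduce. The check has two parts.

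**1. What each described measure can show**

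| Measure | Where | Bears on correctness or completeness? |
|---|---|---|
| Ranking of sources by relevance or importance | 2.1.1 | No |
| Whether information seems trustworthy or unsettling | 2.1.1 | No, this is perception |
| Vegans' DS knowledge (block F), deficiency and dosage (block I) | 2.1.2, 2.5 | Possibly, depending on the items |
| Experts' opinion, knowledge and advice | 2.1, 2.1.1 | Yes, for medical experts only |
| Quality of social media, internet, magazines, social environment | none described | No measure |

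The inference in 2.1.1 uses only the first row. The second row is recorded under the same objective but does not measure adequacy either. The third and fourth rows could support a statement on adequacy, but the sentence does not refer to them. The professional versus informal comparison in 2.7 has no adequacy outcome attached.

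**2. Whether a ranking can locate the main contributor**

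All values here are assumed; none comes from the article. Let source *i* have importance share *s* and let a proportion *q* of its information be inadequate. Its share of all inadequate information is *s*ᵢ*q*ᵢ / Σ *s*ⱼ*q*ⱼ. Take shares A 60%, B 25%, C 15%, so A always ranks first.

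- *q* = A 5%, B 30%, C 10%. Products 0.030, 0.075, 0.015; sum 0.120. A supplies 25%, B 62.5%, C 12.5%.
- *q* = 30% for all. Products 0.180, 0.075, 0.045; sum 0.300. A supplies 60%, B 25%, C 15%.
- *q* = A 0%, B 30%, C 30%. Products 0, 0.075, 0.045; sum 0.120. A supplies 0%, B 62.5%, C 37.5%.

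With B at 30%, A contributes less than B whenever A's rate is below 0.25 × 0.30 / 0.60 = 12.5%. The ranking is identical in all three cases, while the top source supplies 25%, 60% or none of the inadequate information. The deciding quantity is *q*, which the ranking does not hold.

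**The case against.** The strongest reply is that the sentence is rationale and not a method. It says causes could be identified and changed if necessary, which leaves room for a top-ranked source that turns out to be adequate. It can be read as saying only that knowing the important sources shows where to look. This stands in part. A reader might infer that the study will label whichever source ranks first as the cause of inadequacy, whatever its quality. The article contains no such rule, and that reading should not be pressed. But the hedge on change does not repair the stated route from importance to cause.

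A second reply is that adequacy data exist. This also stands: it would be wrong to say that popularity is the study's only input, given the expert survey, the knowledge objective and blocks F and I. The statement in 3.1 on frequency and prevalence does not rule out cross-tabulations or the regressions in 2.7. What remains is that the objective does not rest its conclusion on any of these data, and that no quality measure is described for the non-expert sources.

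A third reply is that pairing sources with outcomes belongs in an analysis plan that is not shown. That is fair for the analysis detail, and section 2.7 allows further comparisons. The point here is the wording of a primary objective, which an analysis plan would not correct.

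Finally, the main-cause phrase in 2.1 concerns literacy, not inadequacy. It is a related case of causal wording and not the same inference.

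**Conclusion.** The concern holds in a limited form and is minor. As worded, the primary objective draws a conclusion about causes of inadequate information from ratings that do not measure adequacy, in a design that cannot establish causes. How far a ranking could mislead cannot be estimated from the article. The illustration shows only that the top source's contribution is undetermined, and its shares and rates are assumptions.

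Two uncertainties limit what can replace the inference. The article gives block headings only, so it is not known whether block F tests knowledge or asks for a self-rating, or whether the source items let respondents be classified by type of source. And no link between individual vegans and individual experts is described in the two anonymous surveys, so the expert results can inform adequacy only at group level.

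**What to change.** 1. In 2.1.1, limit the conclusion from the ranking to identifying the most used and most trusted sources.
2. Rest any statement on inadequate information on those block F and I items that bear on correctness, compared by type of source. This extends the professional versus informal comparison already listed in 2.7, adjusted for the background characteristics named there, with the estimate and its 95% confidence interval. For medical experts, use the expert survey as well.
3. Report importance and adequacy as two separate results, and describe any relation as an association. No significance threshold is needed, since 2.7 treats p-values as descriptive.
4. Replace the causal terms in 2.1.1 (main causes) and 2.1 (main cause) with *factors associated with*.

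The cost is rewording and one extra analysis of items already collected, provided the blocks contain suitable items. Some top-ranked sources may end with no verdict on adequacy.
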